## Abstract

**Background:**

A healthy start to life requires adequate motor development and physical activity participation. Currently 5-15% of children have impaired motor development without any obvious disorder. These children are at greater risk of obesity, musculoskeletal disorders, low social confidence and poor mental health. Traditional electronic game use may impact on motor development and physical activity creating a vicious cycle. However new virtual reality (VR) game interfaces may provide motor experiences that enhance motor development and lead to an increase in motor coordination and better physical activity and mental health outcomes. VR games are beginning to be used for rehabilitation, however there is no reported trial of the impact of these games on motor coordination in children with developmental coordination disorder.

**Methods:**

This cross-over randomised and controlled trial will examine whether motor coordination is enhanced by access to active electronic games and whether daily activity, attitudes to physical activity and mental health are also enhanced. Thirty children aged 10-12 years with poor motor coordination (≤ 15^th ^percentile) will be recruited and randomised to a balanced ordering of 'no active electronic games' and 'active electronic games'. Each child will participate in both conditions for 16 weeks, and be assessed prior to participation and at the end of each condition. The primary outcome is motor coordination, assessed by kinematic and kinetic motion analysis laboratory measures. Physical activity and sedentary behaviour will be assessed by accelerometry, coordination in daily life by parent report questionnaire and attitudes to physical activity, self-confidence, anxiety and depressed mood will be assessed by self report questionnaire. A sample of 30 will provide a power of > 0.9 for detecting a 5 point difference in motor coordination on the MABC-2 TIS scale (mean 17, sd = 5).

**Discussion:**

This is the first trial to examine the impact of new virtual reality games on motor coordination in children with developmental coordination disorder. The findings will provide critical information to understand whether these electronic games can be used to have a positive impact on the physical and mental health of these children. Given the importance of adequate motor coordination, physical activity and mental health in childhood, this project can inform interventions which could have a profound impact on the long term health of this group of children.

**Trial registration:**

Australia and New Zealand Clinical Trials Register (ANZCTR): ACTRN12611000400965

## Background

### Computer use by children is a major change in our society

Nearly all Australian children now use computers and video games [1]. More than 79% of households with children have a computer and more than 60% have a video game machine [2]. A recent meta analysis of studies in affluent countries found boys' and girls' mean computer/video game use was 74 minutes a day [3]. Electronic game use is increasing rapidly, with Roberts et al. [4] reporting a doubling since the meta analysis studies.

In a recent review we [5] reported that the available evidence suggested computer use targeted on learning areas is associated with enhanced academic achievement (e.g. [6]) but that electronic game playing has a negative effect on school achievement [7]. We also found that game-related discourse may provide a stimulus for children's social development [8], although there are concerns about the potential negative effects of violence in electronic games [9].

Research on the impact of computer use on children's physical development has focused on postures during computer use at school [10], use of laptop computers [11] and the impact of workstation design on posture and muscle activity [12]. Whilst this research has suggested potential musculoskeletal problems associated with prolonged and constrained postures and repetitive small movements, there is no evidence available on the impact of computer or electronic game use on motor development. We have raised concerns that electronic game use may have a negative impact on gross motor development as it may displace other childhood leisure activities which provide critical practice of gross motor tasks and which facilitate motor development [5].

### Electronic game use may have a negative impact on normal motor development

Normal motor development requires maturation of neural and muscular systems plus the opportunity to practise fine and gross motor skills, with studies on children with impoverished or enriched motor environments providing evidence for the importance of practice [13]. Gross motor experiences are usually associated with physical activity (PA) (defined as the movement of the limbs and torso by muscle activity resulting in energy expenditure). There is evidence that increased PA can provide the practice necessary to improve gross motor skill development in children with normal motor development [14]. However there are concerns amongst researchers and parents that electronic game playing reduces children's PA.

Traditional electronic game interfaces can provide motor experience, but fine rather than gross. Yuji [15] reported evidence that electronic games improved children's fine motor performance. In a review, Whitcomb [16] found electronic game playing lead to enhanced eye-hand coordination, dexterity and fine motor ability and increased reaction and movement speeds in elderly subjects and Rosser et al. [17] found a dose response relationship between video game experience and laproscopic surgery training performance (both speed and accuracy).

In contrast, traditional electronic game playing probably does not provide gross motor experience, and may lead to a decline in gross motor skill. In an epidemiological study of 1,600 five-year-olds we found that computer use did displace vigorous PA on weekends reducing overall gross motor experience [18] and suggesting a potential vicious cycle.

### Children with DCD are at greater risk

Five to 15% of children have developmental coordination disorder (DCD), defined as lacking developmental, age-appropriate motor skills, and characterised by motor performance impairment that creates functional performance deficits not likely to be due the child's age, intellect, or other diagnosable neurological or psychiatric disorder [19,20]. Underlying deficits identified in children with DCD include poor sensory-motor integration [21] and in particular, poor visuomotor processing [22], or cross-modal integration (visual-kinaesthetic). Children with DCD also have poor timing and force control and it has been argued that there may be a disruption in the central timing mechanisms, usually linked with cerebellar function [23]. A recent review found that these children are less physically active and have lower levels of fitness [24]. Children with DCD are thus at greater risk of insufficient PA [25] and a downward spiral of poorer motor development, psychological and health outcomes (Figure 1).

**Figure 1 F1:**
[figure not shown]
**Vicious cycle of physical activity, motor skill and self esteem**.

### Motor skill can be improved in children with DCD

Whilst there are varying views as to the underlying pathology of DCD and no consensus on the correct approach to intervention, a recent review concluded that there is sufficient evidence of good quality to confirm that interventions are effective in improving motor skill in children with DCD [26]. Approaches ranging from perceptual-motor therapy, to sensory-integration therapy, mastery and physiotherapy are supported with little evidence of the superiority of any specific approach [26], although studies were of variable quality. Intervention doses range from 30 minutes weekly for 6 weeks [27] to 50 minutes 3 times a week for 10 weeks [28].

### Motor skill is important for physical activity participation

Children need to have a certain degree of motor skill to feel confident to engage in PA. Harter's [29,30] competence motivation theory argues that children's motivation to engage in an activity (in this case, PA) is determined partly by the confidence they have in their ability to carry out these tasks. Hence, children who are more skilled would be more likely to engage in the activity. According to Doganis and Theordarakis [31], attitude theory best explains engagement in PA and sport. It is considered to comprise three elements, namely cognitive, affective and behavioural. A child's perception of their own ability is one component of the cognitive element. Their enjoyment of the activity, or the anxiety it generates, are part of the affective element. The behaviour component relates to the outcomes, good or bad, of participation and its reinforcement qualities. Therefore a vicious circle may develop for children where reduced PA results in reduced motor skill which further impedes PA participation.

### Physical activity is important for health and development

Over 80% of Australian children do not meet national standards for adequate PA [32]. A lack of adequate PA has been linked with childhood health issues including obesity, bone mineral density, type II diabetes and cardiovascular risk factors [25,33]. Boys with DCD appear to be at greater risk of obesity [34].

Children with DCD have been found to engage less in PA than other children [25]. More recently Poulsen et al. [35] found a negative correlation between DCD and participation in social PA. It has been suggested that this is due to the fact that children with DCD do not like to display their poorer athletic skill to their peers [34], in line with Harter's [29,30] competence motivation theory. Our research [36] has demonstrated that children with DCD perceive themselves as poorer in the domain of athletic competence, and this has been linked to high levels of anxiety [37] and depressive symptomatology [38]. In line with attitude theory, this negative affect would then impact on the child's future interest in engaging in PA.

### Electronic games have traditionally been sedentary

Electronic games have traditionally used keyboard/mouse and game pad interfaces which require very little movement. In a laboratory study of children with normal motor development we found energy expenditure during traditional electronic game playing to be similar to watching a DVD [39]. We also found minimal levels of muscle activity and movement during traditional electronic game playing [40]. Whilst traditional electronic games may have some positive physical impact on fine motor skills this may be offset by decreasing overall PA levels and reduced gross motor practice. Poorer PA outcomes may be associated with lower activity during actual game playing and by the displacement of more active leisure activities. Reduced gross motor practice may lead to poorer motor development. Whilst Li and Atkins [41] found some evidence of a relationship between poorer gross motor ability and increasing computer use in pre schoolers there is no direct evidence on the link between electronic games and poorer motor skills.

Marshall et al. [42] reviewed available studies and found 10 cross sectional studies showing a weak negative relationship (r = -0.14) between electronic games/computer use and PA. However the nature of computer use was not specified so included games and other uses. Recent reviews have included longitudinal studies and have also questioned whether electronic game use displaces more vigorous PA [43,44]. Despite no experimental evidence of a causal effect of electronic games on motor development, attitudes to PA or overall PA there is considerable community concern.

In a recent pilot study with 12 children (6 with DCD) [45] we found access to traditional electronic games for 8 weeks resulted in a trend for a 23.1% reduction in accelerometer assessed energy expenditure on non school days (p = .122) and significant reductions in both motor competence (McCarron Assessment of Neuromotor Disorders Neurodevelopmental Index [46] 7.3% p = .044) and liking of physical activity [47] (6.0% p = .048) compared to an 8 week period when electronic games were removed from the house of children with DCD (see Figure 2).

**Figure 2 F2:**
[figure not shown]
**Liking of physical activity ratings in children with and without developmental coordination disorder following 8 weeks with no electronic games, 8 weeks with traditional electronic games and 8 weeks with active VR games**.

### New opportunities with active virtual reality games

Virtual reality (VR) refers to a simulated interactive environment. VR aims to create a visual, auditory and sometimes tactile and olfactory environment that appears real and enables the human user to become immersed in the interactive experience. VR has been extensively used in commercial/military training applications such as flight and surgery simulators. It has also been used for arcade games and recently for patient rehabilitation. Until recently the only VR systems were expensive ($100,000+) laboratory based systems or large dedicated leisure simulators. However cheap (< $500) VR systems such as Eye and Move (Sony), Wii (Nintendo) and Kinect (Microsoft) have been released, making VR available to households.

Video capture VR (Eye, Kinect) uses a video camera to capture the user's image and movement and embed this into the virtual environment. Whilst it lacks haptic response and single camera systems (Eye) can only track movement in one plane, it requires no head mounted display or exoskeletion thus enabling movement free of encumbrance. Dual camera systems (Kinect) can track in three dimensions. It also provides a mirror view enabling immediate feedback on posture and quality of movement. Users report the interaction is intuitive and natural, with ratings of sense of presence and enjoyment equalling those of expensive laboratory based systems [48].

### VR electronic games may lead to improved motor skill and PA outcomes

A critical feature of video capture VR games is that it requires arm, leg or whole body movement. It may therefore provide gross motor experiences that are not available when interacting using traditional interfaces such as keyboard, mouse or game pad. Video capture VR may thus enable children to play electronic games without the previously observed detrimental physical effects.

We and others have recently reported significant increases in energy expenditure, heart rate and ventilation volume when children played a game with video capture VR compared to a traditional interface [39,49,50]. Further, trials are being conducted to determine whether VR games in the home can enhance health outcomes for children [51,52].

VR electronic games can enhance motor skill in adults following brain injury with improved locomotion, upper and lower extremity function [53]. VR has demonstrated some improvements in motor performance in case studies of children with cerebral palsy [54]. Wann et al. [55] argue that VR is an ideal tool for remedial programs involving attention and movement disorders, and discuss its use in the context of stroke patients. VR may be particularly successful for children with DCD as it does not require the child to perform in front of other children. Lack of PA in children with DCD has been attributed to their unwillingness to display their poor skill to others. However, VR electronic games may improve these children's skill by providing gross motor practice involving a high level of visual-spatial integration, but in a context which is private, and provides strong motivation by enjoyment of the game and the challenge of self-competition. However this will only occur if the nature of the movement required is suitable.

Improvements in performance in VR are useful if they lead to improvements in real world performance. Whilst there is no available data on this in children, there is evidence of balance gains from VR training resulting in improved real world balance in elderly subjects undergoing rehabilitation [53]. VR training also leads to greater enjoyment of rehabilitation and improved motor confidence in the real world in adults. This suggests VR games could improve real world motor skill in children and could increase children's confidence, which would be additionally beneficial for children with DCD. However, there is no evidence of the effect of VR on children with DCD.

In our recent pilot study involving 6 children with DCD we found access to video capture VR games for 8 weeks tended to increase motor competence (MAND NDI 8.8%, p = .041) as well as accelerometer measured energy expenditure on non school days (54.3% p = .093), compared with access to traditional electronic games in children with DCD and no apparent effect on children without DCD (see Figure 3).

**Figure 3 F3:**
[figure not shown]
**Motor ability (MAND NDI) in children with and without developmental coordination disorder following 8 weeks with no electronic games, 8 weeks with traditional electronic games and 8 weeks with active VR games**.

### Study Aim

Therefore the main aim of this study is to determine whether access to new high fidelity active VR electronic games can enhance motor coordination in children with motor impairment. Secondary aims include investigating whether increases in VR performance translate to increases in real world gross motor performance and increases in physical activity, attitudes to physical activity, self confidence and mental health.

## Methods/design

### Design and Aims

This study will use a cross over randomised controlled trial to assess the impact of active electronic game use on motor coordination and physical and mental health correlates in children with DCD by:

1) Comparing change in motor coordination over 16 weeks when children use active electronic games or no active electronic games. We hypothesise that motor coordination will improve more when children use active electronic games.

2) Comparing change in parent reports of motor coordination during activities of daily living over 16 weeks when children use active electronic games or no active electronic games. We hypothesise that parent reports of motor coordination will improve more when children use active electronic games.

3) Comparing change in physical activity and sedentary behaviour over 16 weeks when children use active electronic games or no active electronic games. We hypothesise that moderate/vigorous physical activity will increase and sedentary time will decrease more when children use active electronic games.

4) Comparing change in attitudes to physical activity over 16 weeks when children use active electronic games or no active electronic games. We hypothesise that attitudes to physical activity will improve more when children use active electronic games.

5) Comparing change in child reports of mental health over 16 weeks when children use active electronic games or no active electronic games. We hypothesise that mental health will improve more when children use active electronic games.

### Sample

30 children (10-12 years of age) will be recruited by mass media, university and school notices and professional networks. This age group has been selected as they are able to provide detailed information in diary and questionnaires, have a high use of electronic games and are developing physical and mental behaviour patterns pre-puberty which may track into adulthood. Children of parents expressing interest will be screened to ensure they are willing to participate after being informed of the full study responsibilities and meet the inclusion and exclusion criteria. Inclusion criteria are: aged 10-12 years at start of study, able to use electronic games on most days and being classified as DCD. DCD status will be assessed using Movement Assessment Battery for Children-2 (MABC-2 [56]. The MABC-2 comprises 8 tasks, three measuring manual dexterity, 3 measuring aiming and catching and 2 measuring balance. Age norms based on a standardisation sample of 1,172 children are used to determine a standard total score (*M *= 10, *SD *= 3). Separate standard scores can be determined for each of the sub-tests. In addition to the total score, a set of qualitative observations allows the examiner to record the child's performance characteristics during the testing. Cut-offs for impairment scores are at or below the 5th percentile for definite motor difficulties, whilst scores above the 5th percentile but at or below the 15th percentile suggest borderline difficulties. The 15^th ^percentile cut off will be used in this study as this is recommended for research purposes to prevent excluding children with mild DCD [57]. Minimum value of the test-retest reliability of the original MABC is 0.75 and the inter-tester reliability is 0.70. The original MABC has been found to correlate well with other movement tests [58,59]. The MABC-2 will be conducted at a location agreed to by parents, typically the child's home. Children will be excluded if they have a diagnosed disorder likely to impact their study participation, movement or electronic game use (other than developmental coordination disorder), live in a shared care arrangement where the child spends a significant amount of time in different houses and is unable to maintain game access condition, or live remote to the University campus. The child's age and sex will be recorded at baseline along with their experience with electronic games and computers using the Young people's Activity Questionnaire [11].

For power calculations, motor impairment (MABC-2 Total Impairment Score) was estimated at 17+5 with a minimum effect size of 5 considered important based on effects in prior studies [60]. If the variation in the motor impairment between repeated time points in each individual is normally distributed with standard deviation 5, and the true effect of game condition is 5, a study with 30 subjects will reject the null hypothesis that this response difference is zero with probability (power) 0.9027. The Type I error probability associated with this test of this null hypothesis is 0.01.

Volunteers and their parents will be provided with a detailed written description of the study purpose, procedures, risks and benefits and given an opportunity to ask research staff for clarification prior to signing assent (children) and consent (parents) to participate. The study has ethical approval from the Human Research Ethics Committee of Curtin University (approval number HR11/2011).

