### Analysis

To examine hypothesis 1 (that motor coordination will be improved when children have access to active electronic games) changes from baseline in laboratory biomechanical and MABC-2 outcomes following both conditions will be compared with a repeated measures ANCOVA analysis with sex as a covariate. A critical alpha level of 0.01 will be used to balance type 1 and type 2 errors.

To assess hypotheses 2, 3, 4, 5 (that parent reports of motor coordination in daily living, physical activity and sedentary behaviour, attitudes to physical activity and measures of mental health will improve when children have access to active electronic games) changes from baseline in outcomes following both conditions will be compared with a repeated measures ANCOVA analysis with sex as a covariate. A critical alpha level of 0.01 will be used to balance type 1 and type 2 errors.

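### The stated power of 0.9027 is a normal-approximation figure; with the same inputs, the t/F test planned for 30 children at alpha 0.01 has power of about 0.86

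*Protocol article*

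**What the plan says.** The power statement is in the Sample section of the protocol article. Its inputs are:

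- Standard deviation: "If the variation in the motor impairment between repeated time points in each individual is normally distributed with standard deviation 5".
- Effect: "the true effect of game condition is 5".
- Type I error: "The Type I error probability associated with this test of this null hypothesis is 0.01".
- Result: "a study with 30 subjects will reject the null hypothesis that this response difference is zero with probability (power) 0.9027".

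The Methods paragraph of the abstract rounds this: "A sample of 30 will provide a power of > 0.9 for detecting a 5 point difference".

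The Analysis section fixes the test as a repeated measures ANCOVA on changes from baseline after the two conditions, with sex as covariate. It repeats the significance level: "A critical alpha level of 0.01 will be used to balance type 1 and type 2 errors".

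The article names neither the power formula nor the number of sides. The null hypothesis is that the difference is zero, so a two-sided test is the natural reading.

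**The concern.** Power is given to four decimals and carried into the abstract as a headline property of the design. A figure quoted that precisely should come from the test that will be run. With 30 children and alpha 0.01, the choice between a normal and a t reference distribution matters. The two-sided critical value is 2.576 for z, but 2.756 on 29 degrees of freedom and 2.763 on 28. A calculation that ignores this overstates power by several points.

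The input is also ambiguous. Variation between repeated time points within a child could mean the standard deviation of each visit's score around the child's own level, or the standard deviation of the change between visits. The two differ by a factor of √2 and lead to very different power, so a reader cannot tell what was assumed.

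At stake is whether the claim of more than 90% power holds under the assumptions that produced it.

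**Working it through.** **Inputs.** n = 30, effect 5, standard deviation 5 and alpha 0.01 (Sample); each child has both conditions (abstract); repeated measures ANCOVA with sex, alpha 0.01 (Analysis). Two-sided testing is inferred from the null hypothesis.

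**Step 1: reproduce the stated figure.** Take 5 as the per-visit within-child standard deviation.

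- SD of the paired difference = 5 × √2 = 7.071
- Noncentrality = 5 / 7.071 × √30 = 3.873
- Normal approximation: Φ(3.873 − 2.576) = Φ(1.297) = 0.9027

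This matches to four decimals. Other calculations for 30 children do not:

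| Calculation | Power |
|---|---|
| One-sided z, difference SD 7.07 | 0.939 |
| One-sided t, 29 df, difference SD 7.07 | 0.9135 |
| Two-sided z, difference SD 5 | 0.998 |
| Two-sided t, 29 df, difference SD 5 | 0.995 |
| Two parallel arms of 15, z / t | 0.565 / 0.500 |

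**Step 2: same inputs, reference distribution of the planned test.** Power is the probability that a noncentral t variable with noncentrality 3.873 exceeds the two-sided 0.01 critical value in absolute size.

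| Error df | Critical t | Power |
|---|---|---|
| 29 (paired t test) | 2.756 | 0.8583 |
| 28 (sex fitted) | 2.763 | 0.8565 |
| 27 | 2.771 | 0.8545 |
| 58 (generous upper case) | 2.663 | 0.882 |

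A simulation of the paired t test with 400,000 trials gave 0.859. The gap from the stated figure is 0.9027 − 0.8583 = 0.044 on 29 df and 0.9027 − 0.8565 = 0.046 on 28 df. The type II error is 1 − 0.858 = 0.142, against the stated 1 − 0.9027 = 0.097.

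**Step 3: the other reading of the standard deviation.** If 5 is the SD of the paired difference, noncentrality = 5 / 5 × √30 = 5.477, and t-based power is 0.995 on 29 or 28 df.

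**Step 4: number of children for 0.90 on the t test, difference SD 7.07.** With 33 completers power is 0.896 to 0.898 (30 to 32 df). With 34 it is 0.907 to 0.909 (31 to 33 df). So 34 are needed.

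**Step 5: illustration of losses.** The calculation uses all 30 children. The article gives no dropout rate, so the completer numbers here are my assumption. With sex fitted, 27 completers give 0.803 (25 df) and 24 give 0.734 (22 df).

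**The case against.** Four points can be made for the plan.

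*The match does not by itself identify the inputs.* A z calculation with difference SD 5 and 15 children has noncentrality √15 = 3.873 and also gives 0.9027. That is true, but it contradicts the stated 30 subjects and is still a normal approximation.

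*If 5 is the SD of the change, the abstract is right.* Power is then 0.995, comfortably above 0.9. This stands as a reading of the sentence. The Sample section's figure would then be wrong in the other direction, because 0.995 is not 0.9027. The shortfall is therefore conditional on the reading that generates the published number.

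*A difference SD of 7.07 is pessimistic.* The article also gives 5 as the spread of the score (mean 17). If 5 is that total SD, a difference SD of 7.07 implies no correlation between two scores from the same child, whereas the article cites a minimum test-retest reliability of 0.75 for the original test. With difference SD = 5 × √(2(1 − ρ)), a correlation of 0.11 gives 6.67 and restores t-based power to 0.900 on 28 df. It is fair to say that actual power may exceed 0.86. But the power sentence assumes no such correlation, and a figure has to follow from its own stated assumptions.

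*The size is modest and dropout is a separate matter.* Power of 0.86 at two-sided 0.01 is respectable. A condensed article may leave an attrition allowance to the full protocol, so the completer figures are illustrative and not a second error.

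The covariate does not rescue the figure. Sex is constant within a child, so it cannot reduce within-child error in the comparison of conditions, and fitting it uses a degree of freedom.

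**Conclusion.** The concern holds. Under the inputs that reproduce 0.9027, the planned two-sided t/F test on 30 children has power of 0.855 to 0.858, about 4.5 points lower, and the abstract's claim of more than 0.9 is not met. Even 58 error degrees of freedom give only 0.882.

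This rests on three things: a two-sided test, 5 as the per-visit within-child SD (difference SD 7.07), and all 30 children completing. That a normal approximation was used is inferred, since no formula is named. The four-decimal match with the stated 30 subjects makes the inference strong. Under the alternative reading of the SD, power is 0.995 and the published figure is wrong the other way.

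The error is one of statement. It does not undermine the design or call for a larger sample.

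**What to change.** In the Sample section and in the abstract, replace the power figure with one from a t-based calculation, and name the method and the two-sided alpha of 0.01.

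- If 5 is the per-visit within-child SD, say so, give the paired-difference SD as 7.07, and state power as about 0.86 with 30 completers. It would help to add the value at a plausible lower number, for example about 0.80 with 27.
- If 5 is the SD of the paired difference, say so and state power as 0.995.

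The cost is two sentences and, on the first reading, a slightly less favourable figure. No extra children are needed. If the sponsor wants to keep the claim of at least 0.90 on the first reading, 34 completers would be required.

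### The stated power of 0.9027 belongs to 30 children who complete both conditions, but 30 is also the number recruited, so it leaves no room for loss over 32 weeks

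*Protocol article*

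**What the plan says.** The Sample section of the protocol article opens with the recruitment target: "30 children (10-12 years of age) will be recruited". The abstract has the same thirty children recruited and randomised to an order of conditions.

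The power paragraph of the Sample section takes the within-child variation in the MABC-2 Total Impairment Score as "normally distributed with standard deviation 5, and the true effect of game condition is 5". It then concludes that "a study with 30 subjects will reject the null hypothesis that this response difference is zero with probability (power) 0.9027", and adds: "The Type I error probability associated with this test of this null hypothesis is 0.01". The Analysis section uses the same level: "A critical alpha level of 0.01 will be used to balance type 1 and type 2 errors". The abstract carries the result without a condition on completion: "A sample of 30 will provide a power of > 0.9 for detecting a 5 point difference in motor coordination".

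The comparison is made within children. According to the abstract, Procedure and Trial flow, each child spends 16 weeks in each condition and is assessed at baseline and at the end of each condition. The Analysis section states that "changes from baseline in laboratory biomechanical and MABC-2 outcomes following both conditions will be compared".

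**The concern.** The same number, 30, serves as the recruitment target and as the number of children in the power calculation. A within-child comparison needs an outcome after each of two consecutive 16-week conditions, so the printed power holds only if all 30 children stay for 2 × 16 = 32 weeks. In that time families must keep active games out of the home for one condition and return to the research centre twice after baseline.

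At stake is how the trial's power is read. The abstract presents power above 0.9 as a property of the recruited sample. If some children do not finish, a null result would be judged against a power that the analysed sample did not have.

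**Working it through.** **Inputs, all from the Sample section**

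- Effect: 5 points.
- Within-child SD per time point: 5, so the SD of a within-child difference is 5 × √2 = 7.07.
- Type I error: 0.01. Sidedness is not stated. The two-sided value, z = 2.576, is the one that reproduces the printed figure.
- n = 30.

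**Reproducing the printed figure**

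Power = Φ(5 / SE − 2.576), with SE = 7.07 / √n.

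At n = 30: SE = 7.07 / 5.477 = 1.291; 5 / 1.291 = 3.873; 3.873 − 2.576 = 1.297; Φ(1.297) = 0.9027. This agrees with the article to four decimals.

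Other readings that were tried do not give 0.9027:

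- one-sided normal approximation: 0.9390
- SD of the difference taken as 5: 0.9981 (normal) or 0.9950 (t)
- paired t test with 29 degrees of freedom: 0.8583
- t with 58 degrees of freedom: 0.8821
- two parallel groups of 15: 0.5647

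The formula for two independent means with 30 per group is algebraically the same as the one used here. On either description, 0.9027 requires 30 outcomes under each condition.

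**Same inputs, fewer children with both post-condition assessments**

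The last column is the exact paired t test (noncentral t, n − 1 degrees of freedom, noncentrality 5 / SE).

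| Complete pairs | SE | 5 / SE | minus 2.576 | Power, normal approximation | Power, paired t |
|---|---|---|---|---|---|
| 30 | 1.291 | 3.873 | 1.297 | 0.903 | 0.858 |
| 29 | 1.313 | 3.808 | 1.232 | 0.891 | 0.842 |
| 28 | 1.336 | 3.742 | 1.166 | 0.878 | 0.825 |
| 27 (10% loss, assumed) | 1.361 | 3.674 | 1.098 | 0.864 | 0.805 |
| 24 (20% loss, assumed) | 1.443 | 3.464 | 0.888 | 0.813 | 0.738 |

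Thirty is therefore the smallest n that reaches 0.90 on the formula behind the printed figure.

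**Size**

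- One child lost: 0.9027 − 0.8910 = 0.0117, about 1.2 percentage points.
- Three lost: 0.9027 − 0.8640 = 0.0387, about 3.9 points.
- Six lost: 0.9027 − 0.8128 = 0.0899, about 9.0 points.
- Moving from the normal approximation to the paired t test with nobody lost: 0.9027 − 0.8583 = 0.0444, about 4.4 points, which is more than the loss of one child costs.

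**The case against.** The strongest reply is that nothing has been miscalculated. The power sentence is conditional on its inputs, says nothing about retention, and is right to four decimals. That stands. A reader might infer from this point that 0.9027 is an arithmetic error; the documents do not support that.

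A second reply is that an article may leave attrition to the full protocol. An unseen retention assumption or replacement rule is possible. But this point does not rest only on something left out: the article prints both the recruitment target and the powered number, and they are equal. An allowance for loss would normally show as a recruitment target above 30.

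Third, 0.90 is nowhere set as a required minimum, and slipping from 0.903 to 0.891 changes no decision. This is also fair. A reader might go further and conclude that the trial is too small or must recruit more. The documents do not support that either: on the article's own formula, power is still 0.813 with 24 completers, at a strict alpha of 0.01.

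Fourth, the loss rates are assumptions, and the protocol takes steps to retain families. It screens for willingness after full explanation, excludes children in shared care who could not keep to the game condition and those living far from campus, and provides regular contact, phone calls and home visits. These measures may keep losses low, but they do not make zero loss a safe planning value.

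Finally, a mixed model could draw some information from a child with only one period. The printed figure, however, is for the comparison with all 30 children contributing under both conditions.

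**Conclusion.** The point holds as a minor correction to how the power is stated. The figure of 0.9027 is right for 30 children with both post-condition assessments. The abstract attaches it to the 30 children recruited, and any loss of complete pairs takes it below 0.90 on the same formula (29 pairs: 0.891).

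The effect is modest for one or two losses and larger at 20% loss. The sizes rest on four things: the article's inputs of effect 5 and within-child SD 5; two-sided alpha 0.01, inferred because it reproduces the figure; an analysis of complete pairs; and assumed loss rates of 10% and 20%. If 5 were the SD of the within-child difference, power would be 0.995 or higher and one loss would not matter, but that reading does not reproduce 0.9027.

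The normal-approximation values should not be restated alone, because a paired t test on the same inputs is already at 0.858 with nobody lost.

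**What to change.** In the abstract and in the power paragraph of the Sample section, state that the power refers to 30 children who complete both conditions with both post-condition assessments. In the Sample section, add the power for a plausible range of completers, labelled as assumed because the protocol gives no attrition rate. On the present inputs these are:

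- normal approximation: 0.903 at 30, 0.864 at 27, 0.813 at 24
- paired t test: 0.858 at 30, 0.805 at 27, 0.738 at 24

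The cost is about two sentences and a less favourable headline figure. Enrolment, design and analysis need not change.
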